### Statistical analysis plan

A fully documented statistical analysis plan (SAP), centred on describing key process measures to decide if a definitive trial is feasible, will be prepared by the statistician (SAP), formally agreed with coinvestigators and the trial steering committee (TSC) prior to data collection being completed. Participant throughput will be summarised in an extended Consolidated Standards of Reporting Trials (CONSORT) diagram.^36^ The CONSORT flow chart will be used to present descriptive data on trial referral, enrolment, intervention allocation, adherence and retention and to document any deviations from protocol.

Feasibility outcomes will be summarised using descriptive statistics, with 95% CIs provided to permit assumptions when planning a future definitive trial. Data relating to referral, screening and enrolment, and recruitment logs will be used to produce accurate estimates of eligibility, consent and recruitment rates.

Treatment assignation, intervention adherence (eg, ACT session attendance) and satisfaction of care data will be used to contribute to the evaluation of the acceptability of randomisation and allocated intervention/treatment arms. At each time point, the time taken (per participant) to complete trial measures will be recorded. Retention rates will also be estimated for each of the patient-reported/clinical outcome measures, with consideration given to differential dropout between the arms of the trial to identify potential (attrition) bias in treatment completion and/or data collection. All feasibility outcomes will be compared with full-trial progression criteria.

Baseline characteristics will be reported according to treatment arm. Continuous variables will be reported as mean (SD) if normally distributed or median (IQR) if non-normal, while categorical variables will be presented as frequency (%). Subsequent analyses will summarise the proposed patient-reported and clinical outcomes (eg, psychological flexibility, subjective memory function, quality of life and depression/anxiety measures) at each time point for each trial arm using appropriate descriptive statistics (eg, group mean, SD). To provide an indication of potential changes in scores/frequencies between the four time points, linear/logistic mixed effects regression models will be employed performed on an intention-to-treat (ITT) basis (accounting for data assumed to be missing at random). These random intercept (mixed) models will include intervention group, time, and intervention group by time interaction. There will be no emphasis on hypothesis testing, however, which is reserved for the future main trial. Rather, pre-to-post-intervention standardised effect sizes (Hedges’ g, relative risk) will be computed (SDs will be computed from estimated model SEs) with associated CIs calculated to explore imprecision around effect sizes.^37^ Due to the small sample size, important covariates (eg, baseline score on relevant measure, gender, age) may be included in models if the two arms happen to be highly imbalanced. ITT analyses will also be administered by imputing values for missing data using a conservative last observation carried forward procedure (given full sensitivity analysis testing of missing data assumptions is beyond the scope of a feasibility study). Exploratory analyses using mixed effect models will examine the rate of change in intervention and control groups on outcome measures across four time points, adjusting for relevant baseline scores and variables of interest (anxiety, depression, subjective evaluation of memory), and investigate changes on a per-protocol basis (focused on intervention adherence; ie, including only participants who attended at least four sessions and with post-treatment data).

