St George’s Hospital in South London, in collaboration with South West London and St George’s National Health Service Mental Health Trust, is a centre of excellence for functional neurological disorders. We have developed a five-session group treatment based on the third-wave CBT known as acceptance and commitment therapy (ACT). This intervention focuses on changing a person’s relationship with their thoughts and feelings. It makes use of mindfulness and acceptance processes and increases values-driven behaviour.^12^ ACT considers psychological inflexibility—behaviour that is driven by attempts to excessively control internal experiences (such as difficult thoughts and feelings)—as a source of emotional distress; hence, its aim is to enhance psychological flexibility.^13^ Psychological flexibility is defined as ‘the ability to contact the present moment more fully as a conscious human being, and to change or persist in behaviour when doing so serves valued ends’^14^ while psychological inflexibility is regarded a transdiagnostic process common to numerous psychopathological states.^15^

Perceived threat is thought to be a maintenance factor for FND. Symptoms, such as cognitive failures in the case of FCD, are experienced as threatening, which causes hypervigilance and autonomic arousal. Symptoms are, therefore, experienced in a ‘top-down’ manner—influenced by cognitive and neurobiological processes of expectations and predictions of illness.^5 16^ Improvement with ACT occurs through six key processes that can be grouped as either ‘mindfulness and acceptance processes’ or ‘commitment and behaviour change processes’.^12^ Consequently, ACT aims to change a person’s relationship with their internal experiences, increasing psychological flexibility and altering the top-down expectations by facilitating bottom-up processes, for example, enhancing connection with direct experiences through mindfulness practices.

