### Recruiting sites and participants

We are recruiting participants from DMCs, NPCs CNCs in London. Recruitment began on 7 November 2022. These different clinics assess a spectrum of patients with cognitive symptoms. DMCs tend to see an older population while younger patients are more often referred to the NPC and CNC. If we are not successful recruiting participants from these sites alone then we will review within the trial management group (TMG) and consider adding additional recruiting sites in nearby specialist clinics.

Clinicians in the recruiting clinics will refer potentially suitable patients to the study team and deliver the ‘TAU’ intervention as part of routine clinical care. Potential participants will provide verbal consent to being contacted by the research team. Following this, they will receive the participant information sheet (see online supplemental appendix 2), including dates of the ACT groups, and the informed consent form (see online supplemental appendix 3) and given at least 24 hours to consider these. The consent form will also record whether participants are willing to be contacted about involvement in a parallel qualitative study, described below. Potential participants will be informed that choosing not to take part will not impact their medical treatment with any service. Once consent is given, the research assistant contacts the potential participant to complete a screening interview against the inclusion/exclusion criteria (see figure 1).

10.1136/bmjopen-2023-072366.supp2Supplementary data

10.1136/bmjopen-2023-072366.supp3Supplementary data

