### The ACT intervention

The group consists of psychoeducation about normal memory functioning, including the roles of attention and normal patterns of forgetting. The psychoeducation element aims to reduce the threat of cognitive symptoms. In line with the ACT model, the aim is to increase psychological flexibility (our proposed primary clinical outcome measure for a future RCT; AAQ-II) in response to the symptoms and associated thoughts and feelings.

The concept of ‘secondary suffering’ is introduced.^32^ It is suggested that attempts to control cognitive ‘failures’ leads to additional suffering, such as ruminations, negative predictions and avoidance. It is explicitly stated that the intervention does not aim to reduce ‘primary suffering’ (the cognitive symptoms), although it is possible that improvements may occur if secondary suffering is reduced. Brief mindfulness practices are incorporated in the group to facilitate ‘bottom-up’ processing, acceptance and more neutral interpretations of unwanted experiences. Value-based goals are identified throughout the sessions in order to shift away from avoidance-based behaviour and the focus on cognitive symptoms.

Participants will be given the time of all ACT sessions prior to randomisation and are asked to consent only if able to attend should they be randomised to the active intervention. They will sent an email with link and diary invite for all the sessions the week before the first session and follow-up reminder calls/emails each week to maximise attendance and engagement despite their memory problems. If a participant fails to attend a session, they will receive a follow-up call from the research assistant to ensure they had the time and link and to enquire about future attendance.

The intervention protocol (see online supplemental appendix 4) will be amended in response to specific feedback received during the contemporaneous qualitative interviews which are designed to explore the participants experience of and satisfaction with the groups.

10.1136/bmjopen-2023-072366.supp4Supplementary data

The intervention group will also receive TAU, as below.

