### The qualitative study

A subsample of participants in both arms of the trial will be invited for in-depth semistructured interviews over the course of the intervention period. A sampling framework will be used that ensures participants are included that are representative of the sociodemographic characteristics and clinical profile. Interviews at baseline (T0) will focus on the experience of living with FCD and subsequent interviews (at T1), not necessarily with the same participants, will explore their views on the ACT intervention. These interviews will focus on the acceptability, number, and frequency of ACT sessions, ways of optimising engagement, perceived benefits/limitations of the intervention, and any recommendations for improvement of the components and/or content of the intervention.

Interview schedules will be coproduced by the patient and public involvement (PPI) representatives and the research team. One-to-one, in-depth interviews will be carried out via teams by the research assistant, recorded and transcribed, and the transcripts cross-checked against the original recordings to ensure accuracy. The analysis will be led by the qualitative study expert and research assistant using reflexive thematic analysis^38^ aided by NVivo V.12 software. The results of the T1 interviews will be used to optimise the intervention during the feasibility study with the aim of developing a formalised intervention to be used in a future RCT.

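### ACT is delivered in groups and TAU is not, but neither the stated models nor the ACT-arm precision figure allows for therapy-group clustering, so the intervals will be too narrow if the within-group correlation is positive

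*Protocol article*

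**What the plan says.** The Introduction describes the intervention as a group therapy: "We have developed a five-session group treatment based on the third-wave CBT". Recruiting sites and participants refers to more than one group, since the information sheet is sent "including dates of the ACT groups". How many groups there will be, and how large, is not stated. Under Treatment as usual, the control condition is explanation, information and signposting by the recruiting service, with no group sessions.

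The Statistical analysis plan section names the model terms: "These random intercept (mixed) models will include intervention group, time, and intervention group by time interaction". The level of the random intercept is not named. With four repeated measurements per person, participant level is the natural reading. SDs for the standardised effects are to be derived from the model standard errors, "with associated CIs calculated to explore imprecision around effect sizes". The same section says that feasibility outcomes get 95% CIs to support planning of the definitive trial.

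The Sample size section gives 16.0% as the width of the 95% CI for an 80% adherence rate in the treatment arm (24 patients). Therapy group, clustering and ICC appear nowhere in the article.

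**The concern.** Members of one ACT group share sessions, peers and dates, so their outcomes and attendance may be correlated. TAU patients have no such grouping. This is a partially nested design, with clustering in one arm only. A model with only a participant-level intercept accounts for repeated measures on the same person, but not for correlation between people in the same group.

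The intervals are what is at stake. The plan gives them a definite job: to show how imprecise the effect sizes and feasibility rates are when the next trial is designed. Adherence, satisfaction and a signal on psychological flexibility are also progression criteria, so intervals that look tighter than they are could lend those results more certainty than 24 grouped patients can support.

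**Working it through.** **Inputs from the article.** 48 patients, 24 per arm; 80% adherence in the ACT arm; stated precision 16.0% (Sample size).

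**Assumed inputs.** Equal groups of size m and a therapy-group ICC, neither of which is given. The same ICC is used for continuous outcomes and for binary attendance, which is a further assumption.

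**Step 1. Reproduce the stated figure.** Under independence, 1.96 × √(0.80 × 0.20 / 24) = 0.160, or 16.0 points. This is the half-width; the full width is 32.0 points. No clustering allowance is included.

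**Step 2. Design effect in the ACT arm.** DE = 1 + (m − 1) × ICC.
- m = 6, ICC 0.05: 1 + 5 × 0.05 = 1.25; effective n = 24 / 1.25 = 19.2.
- m = 8, ICC 0.10: 1 + 7 × 0.10 = 1.70; effective n = 24 / 1.70 = 14.1.

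**Step 3. Between-arm standard error.** With equal arms, equal total variance and clustering in one arm only, the true SE divided by the independence-based SE is √((DE + 1) / 2).
- DE 1.25: √1.125 = 1.06.
- DE 1.70: √1.35 = 1.16.

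The true SE is thus 6 to 16% larger than the reported one. Equivalently, the reported SE is 6 to 14% too small (1 − 1/1.06 = 0.06; 1 − 1/1.16 = 0.14). Coverage of a nominal 95% interval falls to 93.5% and 90.8% respectively.

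**Step 4. Adherence half-width.** 16.0 × √DE gives 16.0 × √1.25 = 17.9 points and 16.0 × √1.70 = 20.9 points.

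**Step 5. Wider range of assumptions** (m = 4 to 12, that is, 6 to 2 groups):

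| ICC | DE | Between-arm SE factor | Adherence half-width (points) |
|---|---|---|---|
| 0 | 1.00 | 1.00 | 16.0 |
| 0.01 | 1.03–1.11 | 1.01–1.03 | 16.2–16.9 |
| 0.05 | 1.15–1.55 | 1.04–1.13 | 17.2–19.9 |
| 0.10 | 1.30–2.10 | 1.07–1.25 | 18.2–23.2 |
| 0.20 | 1.60–3.20 | 1.14–1.45 | 20.2–28.6 |

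**Step 6. Could this trial estimate the ICC?** The one-way ANOVA estimator was simulated with a true ICC of 0.05 (40,000 replicates). The central 95% range of the estimate was −0.26 to 0.44 with six groups of 4, −0.18 to 0.41 with four of 6, −0.14 to 0.40 with three of 8, and −0.09 to 0.41 with two of 12. Between 45% and 56% of estimates were zero or below.

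**The case against.** The strongest reply is that little depends on these intervals. The article says "There will be no emphasis on hypothesis testing, however, which is reserved for the future main trial", and no progression criterion is defined by an interval: recruitment, adherence and satisfaction are thresholds on rates, and the efficacy signal has no interval rule. This stands as a limit on the consequence. It does not remove the point, because the intervals are still meant to convey imprecision for planning.

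A second reply is that a full analysis plan will follow and may deal with clustering. That holds for matters the article leaves open, such as which tables to print or whether to report an ICC. It does not cover the model terms, which the article states.

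Three stronger readings are tempting, and the documents do not support them.
- *The intervals are certainly too narrow.* This needs a positive ICC, and none is given. Shared facilitators add between-group variation only if facilitators differ between groups, which is not stated.
- *The definitive trial loses an ICC it needs.* The analysis plan is not shown and could include one. Step 6 shows that an estimate from 2 to 6 groups would be nearly uninformative, so little would be lost.
- *Amending the intervention is part of the clustering fault.* The manual "will be amended in response to specific feedback received during the contemporaneous qualitative interviews", and The qualitative study adds: "The results of the T1 interviews will be used to optimise the intervention during the feasibility study". This is an open aim of the study. It makes the ACT effect an average over versions, with version tied to calendar time and partly to group. That is a separate matter, which a random group effect would not resolve.

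**Conclusion.** The point holds conditionally. On the natural reading of the random intercept as participant-level, the stated models ignore therapy-group clustering in the ACT arm, and the stated adherence precision ignores it too. With 6 to 8 patients per group and an ICC of 0.05 to 0.10, the understatement is moderate: 6 to 16% on the between-arm SE, and about 2 to 5 points on the adherence half-width (17.9 − 16.0 = 1.9; 20.9 − 16.0 = 4.9). Satisfaction intervals in the ACT arm would widen by the same factor, √DE, for the same ICC. With an ICC of 0.01 or below the effect is negligible, and at zero nothing changes. No progression threshold as written would move. This is a worthwhile correction to how uncertainty is reported. It is not a flaw in the trial's design or a reason to change its conduct.

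**What to change.** - Carry a therapy-group identifier and a manual-version identifier in the analysis data.
- Keep the stated model. Beside it, report sensitivity intervals with the ACT-arm variance inflated at fixed ICCs, for example 0.01, 0.05 and 0.10, for AAQ-II and the other effect sizes, adherence and satisfaction. State the group sizes used.
- Where it converges, also fit a partially nested model with a group random effect in the ACT arm only and small-sample degrees of freedom. In that model, take the SDs for Hedges' g from the variance components. Back-calculating them from standard errors assumes independent patients.
- Tabulate attendance, satisfaction and AAQ-II by group and manual version. Present any ICC as descriptive only, with its interval.

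The cost is some analysis-plan wording and two identifiers the team should already hold, and the resulting intervals will be slightly wider. The article has the analysis plan agreed before data collection is completed, so the change fits its own timetable.

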### Secondary (clinical) outcome measures

Those who are deemed eligible to participate in the trial will be sent an individualised weblink to complete baseline (T0) clinical outcome measures. These can be completed on paper if the participant prefers. The paper forms will be returned to the research assistant for inputting into the online database and then securely destroyed.

Clinical outcome measures will be completed at baseline (T0) and at 8 weeks (T1), 16 weeks (T2) and 26 weeks (T3). The proposed clinical outcome measures and the domains being measured include:

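### In models that keep T0 as a response, adding the baseline score when arms look imbalanced barely moves the pre-to-post contrast; baseline adjustment should be built in and pre-specified

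*Protocol article*

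**What the plan says.** The Statistical analysis plan section sets out linear or logistic mixed models to describe "potential changes in scores/frequencies between the four time points". The section on secondary (clinical) outcome measures gives those times as T0, 8, 16 and 26 weeks, so the baseline score is itself one of the modelled responses.

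On the terms: "These random intercept (mixed) models will include intervention group, time, and intervention group by time interaction". The group term is free, and nothing constrains the two arms to share a mean at T0. The quantities to be reported are "pre-to-post-intervention standardised effect sizes" with confidence intervals.

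On adjustment in these models: "important covariates (eg, baseline score on relevant measure, gender, age) may be included in models if the two arms happen to be highly imbalanced". No threshold for high imbalance is given.

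The exploratory models adjust for baseline without any trigger, but over the same set of times: "across four time points, adjusting for relevant baseline scores and variables of interest".

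**The concern.** Two features do not fit together. First, whether to adjust for baseline is left to discretion after the arms have been compared. Second, the adjustment is a person-level covariate in a model that, as described, already has the baseline score among its responses. The pre-to-post effect in such a model is a within-person comparison, and a covariate that is constant within a person has almost no purchase on it. The step meant to deal with imbalance would then leave the reported effect essentially where it was.

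What is at stake is precision, and the accuracy of the estimate in the particular trial obtained. With 24 per arm, chance imbalance at T0 is not small. The effect sizes and intervals are a stated product of the study, and the AAQ-II, on which the efficacy signal is based, is the potential primary outcome of the definitive trial.

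**Working it through.** The article gives no figure for the precision of the clinical effect, so there is none to reproduce.

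**Inputs.** From the article: 24 per arm (Sample size); four times including T0; random intercept, group, time and group-by-time. Assumed: outcome SD of 1, a common correlation rho between T0 and each follow-up (the pattern a random intercept implies), and time as a categorical factor.

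**Step 1: what the contrast is.** With complete data the T3 group-by-time term is (ACT mean at T3 − ACT mean at T0) − (TAU mean at T3 − TAU mean at T0). A covariate b for person i adds the same amount, beta × b, at all four times and cancels from that person's change. It can alter the group main effect but not the interaction.

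**Step 2: numerical check, complete data.** Random-intercept models were fitted by REML to simulated trials with and without the baseline covariate:

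| rho | T0 imbalance | T3 contrast (SE), no covariate | with covariate | Post-score ANCOVA |
|---|---|---|---|---|
| 0.4 | −0.490 | 1.0312 (0.3053) | 1.0312 (0.3053) | 0.741 |
| 0.6 | −0.406 | 0.7897 (0.2519) | 0.7897 (0.2519) | 0.676 |
| 0.8 | 0.032 | 0.6413 (0.1908) | 0.6413 (0.1908) | 0.648 |

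Each contrast equals the difference in change computed by hand.

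**Step 3: missing data.** In 60 simulated trials at rho 0.6 with about 15% of records missing, the covariate moved the estimate by 0.03 SD on average (maximum 0.06). Mean SE went from 0.292 to 0.282, against 0.269 with arm means constrained equal at T0. A single trial at rho 0.4 with 50 of 192 records missing moved by 1.1789 − 1.0851 = 0.09, with SEs of 0.37 to 0.39.

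**Step 4: cost of leaving change unadjusted.**

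- Variance of the change contrast: 2(1 − rho) × 2/24.
- Variance of the baseline-adjusted estimate: (1 − rho²) × 2/24.
- SE ratio: sqrt(2/(1 + rho)).
- Chance imbalance at T0 has SD sqrt(2/24) = 0.29.
- Given an imbalance d, the change contrast is off by −(1 − rho) × d, because it subtracts all of d where only rho × d is expected to persist.

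| rho (assumed) | SE, change | SE, adjusted | Ratio | Size of error at d = 0.29 |
|---|---|---|---|---|
| 0.4 | 0.316 | 0.265 | 1.20 | 0.17 |
| 0.5 | 0.289 | 0.250 | 1.15 | 0.14 |
| 0.6 | 0.258 | 0.231 | 1.12 | 0.12 |
| 0.7 | 0.224 | 0.206 | 1.08 | 0.09 |
| 0.8 | 0.183 | 0.173 | 1.05 | 0.06 |

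The variance ratio (1 + rho)/2 is 0.70, 0.80 and 0.90 at rho 0.4, 0.6 and 0.8, equivalent to giving up 30%, 20% and 10% of participants.

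**Step 5: behaviour when arms are imbalanced.** Over 20,000 simulated trials (rho 0.6, true effect 0.40), those with imbalance above 0.4 SD had a mean imbalance of 0.532. The change contrast averaged 0.19 in them, matching 0.40 − 0.4 × 0.532 = 0.187. ANCOVA averaged 0.40.

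**The case against.** The best reply has four parts.

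- **The covariate is not inert in every setting.** A reader might infer that it never does anything. The article does not support that: it plans for data missing at random and for logistic models as well as linear ones. With missing data the estimate and SE do shift a little, and logistic models were not assessed. The between-arm difference at a visit (group plus interaction) also responds: in the rho 0.6 example it moved from 0.384 to 0.664, close to the ANCOVA value of 0.676. This limits the point to the pre-to-post contrast, which is the effect that the article names, though it does not spell out the contrast behind Hedges' g.
- **Imbalance is not ignored, and the estimate is not biased.** A reader might infer either. In fact the change contrast removes the whole imbalance, which is too much, and it is unbiased over randomisations. The conditional error is already part of its larger SE and is not a second harm.
- **The article does not say that T0 stays in the response when the baseline score enters the main model.** That is true, and the promised SAP could settle it. The exploratory sentence, however, does place baseline adjustment alongside four time points, and the data-driven rule is stated outright in the article.
- **This is a feasibility study, with testing left to the main trial.** It would go too far to say that progression turns on this: the efficacy criterion has no numeric threshold and is not tied to this model. But the point concerns estimates and intervals, which the article does promise.

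**Conclusion.** The concern holds in this form. If T0 remains a response, the planned baseline covariate leaves the linear pre-to-post contrast and its SE exactly unchanged with complete data, and nearly unchanged with moderate missingness. The contrast stays an unadjusted difference in change: valid, but less precise than it need be and over-corrected for imbalance. The size is moderate and depends on a correlation that the article does not give. It also rests on the equal-correlation pattern, on 24 analysed per arm and on linear models. The last-observation-carried-forward analysis gives every participant with a T0 score a full set of values, so for linear models there the exact result applies.

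**What to change.** Replace the discretionary rule for the baseline score with pre-specified adjustment for every outcome measured at T0. There are two ways:

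- **Preferred:** keep all four time points and constrain the arm means to be equal at T0 (drop the group main effect and keep a group term at each follow-up). This retains everyone with any data, in line with the intention-to-treat basis.
- **Alternative:** model T1 to T3 only, with the T0 score as a covariate plus group, time and group-by-time. This drops participants with no follow-up and uses one degree of freedom.

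Use the same structure in the exploratory models. Deleting only the imbalance condition would not be enough, because the permissive wording would leave adjustment wholly discretionary. For gender and age, either pre-specify them as covariates or omit them. State separately how baseline enters the logistic models.

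The cost is SAP wording, settled before the SAP is agreed. No new data are needed.

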### Primary outcome measures and progression criteria

The feasibility study is primarily gathering data on the feasibility of conducting a future definitive RCT. The primary outcome measures (and progression criteria) are:

Rate of successful recruitment (≥70% intended participants recruited).Rate of successful adherence (≥75% in ACT+TAU attend four or more sessions).Acceptability of the ACT intervention (qualitative interview themes and majority (≥75%) satisfied/very satisfied on 5-point Likert scale).Signal of efficacy (based on increased psychological flexibility following intervention).

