### Treatment as usual

TAU was selected as the fairest comparison, given that is what most patients in the UK currently receive within mental health and cognitive neurology settings. It consists of an explanation of the FCD diagnosis, provision of additional information about the diagnosis and underlying factors (such as medications, chronic pain or poor sleep hygiene; information: https://www.neurosymptoms.org/en/symptoms/fnd-symptoms/functional-cognitive-symptoms), and signposting to local psychological services in primary care (IAPT) for appropriate treatment, such as CBT, when comorbid anxiety and/or depression have been identified. TAU will be delivered as part of routine clinical care by the recruiting service.

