### Sample size

This is a feasibility trial; as such, a power calculation is neither possible nor necessary. Rather, the sample size is pragmatic. Target recruitment is 48 patients in total (24 in each treatment arm), which provides sufficiently reliable estimates of feasibility outcomes such as recruitment, adherence and retention rates to inform a fully powered RCT. For example, assuming 70% of those approached consent to participate in the trial, the 95% CI for adherence rate would have width of 13.0%. For those in the treatment arm, the 95% CI for an intervention adherence rate of 80% would have width of 16.0%. A sample size of 48 is also consistent with those recommended for pilot and feasibility studies to provide adequate data and precision of means and variances (n between 24 and 50).^33–35^ If it proves challenging to recruit participants via these routes alone then we will approach colleagues at other specialist services in London who see patients with FCD to increase our recruitment pool.

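### LOCF is called conservative and is the only check on the missing-at-random model, but it can overstate or understate the 26-week effect; the per-protocol set also needs a rule for TAU

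*Protocol article*

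**What the plan says.** All of this is in the Statistical analysis plan section of the protocol article unless another section is named.

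- The main analysis of clinical outcomes is a random-intercept mixed model by intention to treat, described as "accounting for data assumed to be missing at random".
- Intention-to-treat analyses will also be run by "imputing values for missing data using a conservative last observation carried forward procedure". The reason given for going no further is "given full sensitivity analysis testing of missing data assumptions is beyond the scope of a feasibility study". No other check on missing data is named.
- Exploratory mixed models will "examine the rate of change in intervention and control groups on outcome measures across four time points", and will also look at change on a per-protocol basis, "including only participants who attended at least four sessions and with post-treatment data".
- Sessions exist only in the ACT arm. The adherence criterion under Primary outcome measures and progression criteria is "≥75% in ACT+TAU attend four or more sessions". The Treatment as usual section says of TAU: "It consists of an explanation of the FCD diagnosis, provision of additional information about the diagnosis and underlying factors", plus signposting where needed.
- Table 1 marks the intervention as completed at T1 (8 weeks). Outcomes continue to T2 (16 weeks) and T3 (26 weeks).

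**The concern.** Calling LOCF conservative tells the reader that its result is a floor for the benefit. The article gives no argument for this, and the design gives a reason to doubt it: treatment stops at T1 and follow-up runs a further 18 weeks (26 − 8). Any fading of benefit is hidden for ACT participants who leave after T1. LOCF is also the only named companion to the missing-at-random model. If it is taken as a lower bound, the definitive trial could be planned on an effect that is too large or too precise.

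The per-protocol definition raises a smaller problem. It is a session-attendance rule with no counterpart in TAU, set in a sentence about both arms. The article does not say whether TAU participants are in the set.

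**Working it through.** The article states no figure on this point, so there is nothing to reproduce. It gives no dropout rate and no expected trajectory. The check is therefore on direction, under labelled assumptions.

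**LOCF, effect at T3.** Let improvement be in SD units from baseline, with dropout unrelated to outcome within arm. The expected LOCF difference is the sum over visits of (share of ACT last seen at that visit × ACT mean there), minus the same sum for TAU.

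Assume TAU is flat at 0, ACT gains 0.5 at T1 fading to 0.2 at T3, and 25% of ACT is lost. The true T3 effect is 0.20.

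- All loss between T1 and T2: 0.75 × 0.2 + 0.25 × 0.5 = 0.275, which is 0.275/0.20 = 1.38 times the truth.
- 15% lost before T1 and 10% between T1 and T2: 0.75 × 0.2 + 0.15 × 0 + 0.10 × 0.5 = 0.20, no bias.
- All loss before T1: 0.75 × 0.2 + 0.25 × 0 = 0.15, an understatement.

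Other assumed courses:

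- Gain sustained at 0.50, TAU flat, 20% loss per arm, half of it before T1: (0.05 + 0.05 + 0.80) × 0.5 = 0.45 against 0.50, an understatement. It comes from the 10% lost before T1; with no loss before T1, LOCF would return 0.50.
- Gain 0.50, 0.30, 0.10 at T1, T2, T3, with 10% last seen at T1 and 10% at T2: 0.1 × 0.5 + 0.1 × 0.3 + 0.8 × 0.1 = 0.16 against 0.10.
- No effect, both arms improving 0.2, 0.35, 0.5, with 10% loss in ACT and 30% in TAU. Shares last seen at T1, T2, T3 are 0.03, 0.02, 0.90 in ACT and 0.10, 0.05, 0.70 in TAU, the rest at baseline. ACT: 0.03 × 0.2 + 0.02 × 0.35 + 0.90 × 0.5 = 0.463. TAU: 0.10 × 0.2 + 0.05 × 0.35 + 0.70 × 0.5 = 0.3875. Difference: +0.076. With the dropout rates exchanged, it is −0.076.

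**LOCF, precision.** There are 24 per arm (Sample size section). With 25% of ACT lost, 18 are observed at T3 but 24 are analysed as if observed. With TAU complete, the ratio of nominal to honest standard error for the difference is sqrt[(1/24 + 1/24)/(1/18 + 1/24)] = 0.926, about 7% too small. This is an upper figure for the example, since it takes a carried-forward score to hold no information about T3.

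**Per-protocol set.** There are two readings.

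- Literal: at 75% attendance, 18 of 24 ACT participants meet the session rule and 0 of 24 TAU participants do. Only an ACT before-after change is left, with no control for natural change.
- Session rule applied to ACT only: selected attenders are compared with unselected TAU. With no true effect, the spurious difference is rho × phi(c)/q, where q is the share attending four or more sessions, c is the normal quantile at 1 − q, and rho is the correlation of attendance propensity with outcome change. At q = 0.75 it is 0.085, 0.127 and 0.212 SD for rho = 0.2, 0.3 and 0.5. At q = 0.80 it is 0.070, 0.105 and 0.175 SD. It is 0 if rho = 0.

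**The case against.** The best defence is that LOCF may well be conservative in this trial. The Introduction cites a cohort in which cognitive symptoms persisted in 85% over an average of 20 months, which makes a flat TAU course plausible. With a lasting ACT gain and some early loss, LOCF shrinks the effect. That stands, although the figure concerns cognitive symptoms and not psychological flexibility, and it says nothing about whether an ACT gain lasts.

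A reader might infer that LOCF favours ACT here. The documents do not support that: neither fading nor the timing of dropout is given, and moving the loss before T1 reverses the sign. Nor should a 13% shortfall in standard error (sqrt(18/24) = 0.866) be read as the error in the treatment comparison. In the example it applies to the ACT mean alone.

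The role of these analyses is also limited. The main model is intention to treat, hypothesis testing is not emphasised, differential dropout will be examined, and the per-protocol work is labelled exploratory. A signal of efficacy is among the progression criteria but is not tied to either analysis. A reader might infer that the per-protocol set both excludes all of TAU and biases the arm comparison towards ACT. Those belong to different readings and cannot both hold. The full SAP may settle which is meant.

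What remains is that the article itself fixes LOCF as its one check and asserts an unconditional property that LOCF does not have.

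**Conclusion.** The point holds in a limited form. LOCF cannot be called conservative without conditions: in the fading example, with 25% of ACT lost, the T3 estimate runs from 0.15 to 0.275 SD around a true 0.20 depending only on when participants leave, and under unequal dropout it can take either sign when there is no effect. Intervals can also be too narrow, by up to about 7% in the between-arm standard error with TAU complete. All these sizes rest on assumed trajectories and dropout. The conclusion that the direction is not guaranteed needs only that fading, early loss and unequal loss are all possible.

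The main analysis is unaffected. The change is worth making because LOCF is the only named check on that analysis. The per-protocol point is secondary: a definition to clarify in an exploratory analysis.

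**What to change.** 1. Delete the word *conservative* and keep the missing-at-random mixed model as the main analysis.
2. Replace LOCF with one simple departure from missing at random: either a fixed worsening added to imputed ACT values (a delta shift), or reference-based multiple imputation in which ACT participants lost to follow-up take the TAU trajectory. One such check is well short of the full sensitivity testing that the article rules out.
3. State whether the per-protocol analysis is a within-ACT description or a comparison of ACT attenders with TAU, and in the latter case which TAU participants are included. Report it as descriptive and non-randomised.
4. A complier-average estimate (intention-to-treat difference divided by the share attending four or more sessions) is optional. It assumes that fewer than four of the five sessions do nothing, and it overstates benefit if partial attendance helps. For example, if 80% attend and gain 0.5 SD and the rest gain 0.3 SD, the intention-to-treat effect is 0.8 × 0.5 + 0.2 × 0.3 = 0.46, and 0.46/0.8 = 0.575, which is 15% above the attenders' true 0.5.

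The cost is a change of wording and a little analysis code, with no new data. The downside is somewhat wider intervals.
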